
### **5.1.2      Standard Radiation Therapy**

External beam RT should begin  $4 \pm 2$  weeks after histopathologic diagnosis of a WHO Grade III or IV high grade glioma and will be given under the direction of the study Radiation Oncologist, [name]., Ph.D., or his designate, at Duke University or another institution. One treatment of 1.8 Gy will be given daily, 5 days per week, (*33 fractions over less than seven weeks*) for a total of 59.4 Gy. All portals shall be treated during each treatment session. Doses are prescribed at the maximum isodose line encompassing the target volume. Treatment shall be delivered on megavoltage machines of energy ranging from 4 to 18 MV photons. Selection of the appropriate photon energy(*ies*) should be based on optimizing the RT dose distribution within the target volume and minimizing dose to non-target normal tissue. Photon energies > 10 MV should be utilized only in dual energy beam arrangements using at least one beam with energy < 10 MV. Source skin distance for SSD techniques or source axis distance for SAD techniques must be at least 80 cm.

The patient shall be treated in the supine or another appropriate position for the location of the lesion. A head-holding device that is transparent to x-rays and provides adequate immobilization must be utilized at all times during planning and therapy to ensure reproducibility.

The initial target volume shall include the contrast-enhancing lesion and surrounding edema (*if it exists*) demonstrated on pre-operative MRI plus a 2.0-cm margin. If no surrounding edema is present, the initial target volume should include the contrast-enhancing lesion plus a 2.5-cm margin. This primary target volume will be treated to 50.4 Gy in 28 fractions, at 1.8 Gy per fraction.

The boost volume will be based on the post-surgical MRI. After 50.4 Gy, the boost volume will include the contrast-enhancing lesion plus a 1.5-cm margin or, if minimal contrast-enhancing lesion is present at a portion of the resection cavity on MRI, the surgical defect plus a 2.0-cm margin, whichever is greater at that segment of the MRI image. The boost volume will be treated to an additional 9.0 Gy in 5 fractions, 1.8 Gy per fraction. This will bring the total target dose to 59.4 Gy in 33 fractions. All parts of the target volumes are to receive at least 100% but no more than 110% of the dose at the prescription isodose line.

Treatment plans may include opposed lateral fields, a wedge pair of fields, rotation, or multiple-field techniques. MRI-guided 3D treatment planning is necessary to assure accuracy in the selection of field arrangements. Isodose distributions for the primary and boost target volume are required on all patients, including those treated with parallel-opposed fields. A composite plan is required showing the respective target volumes. The inhomogeneity across the target volume shall be kept to a minimum. The maximum dose should be no higher than 10% of the dose at the prescription isodose line. The lens and cervical spine must be shielded from the direct beam at all times. The maximum dose to the optic apparatus (optic chiasm, optic nerves, eyes) must be limited to 54 Gy, and the brain stem to 60 Gy.

### 5.1.3 **Temozolomide Therapy**

TMZ will be administered concomitant with standard external beam RT under the direction of the study Neuro-Oncologists (listed on title page), or their designates, respectively, at Duke University or another institution at a dose of 75 mg/m^2/d, given 7 days per week from the first day of RT until the last day of RT, but for no longer than 49 days. Dose reduction or alteration during this period due to toxicity will be performed as outlined in Table 1.

| Table 1: Temozolomide Dosing Interruption or Discontinuation During Concomitant Radiotherapy                                                                                                                                                                                                              |                                    |                           |
|------------------------------------------------------------------------------------------------------------------------------------------------------------------------------------------------------------------------------------------------------------------------------------------------------------------|------------------------------------|---------------------------|
| Toxicity                                                                                                                                                                                                                                                                                                         | TMZ Interruption a      | TMZ Discontinuation       |
| Absolute Neutrophil Count                                                                                                                                                                                                                                                                                        | ≥0.5 and <1.0 x 10  /L | <0.5 x 10  /L |
| Platelet Count                                                                                                                                                                                                                                                                                                   | ≥10 and <100 x 10  /L  | <10 x 10  /L  |
| Common toxicity criteria (CTC  ) Non-hematological Toxicity (except for alopecia, nausea, vomiting)                                                                                                                                                                                                 | CTC Grade 2                        | CTC Grade 3 or 4          |
| a: Treatment with concomitant TMZ could be continued when all of the following conditions were met: absolute neutrophil count ≥1.0 x 10  /L; platelet count ≥100 x 10  /L; CTC non- hematological toxicity ≤Grade 1 (except for alopecia, nausea, vomiting). |                                    |                           |

If interrupted, TMZ may be resumed when re-treatment criteria are met (Table 1). However, if there is a >2 week delay to resume TMZ, the dose will be modified as outlined in Table 2.

| Table 2: Dose Modifications of Temozolomide during Radiation Therapy |                      |
|-----------------------------------------------------------------------------|----------------------|
| Dose at Toxicity                                                     | Modified Dose |
| 75 mg/m  (during XRT)                                           | 60 mg/m  |
| 60 mg/m  (during XRT)                                           | 50 mg/m  |

Patients who require a dose modification below 50 mg/m^2 during RT will have TMZ held for the duration of external beam RT, but will be able to resume TMZ following completion of external beam RT and will not be excluded from the study.

Once radiation is complete and following a 3 ± 1 week break to allow patients meet criteria to resume TMZ (Table 3), patients will receive a total of 6 cycles of TMZ according to the 21-day schedule at a target dose of 100 mg/m^2/d. Standard dose 21-day TMZ treatment at a target dose of 100 mg/m^2/day is recommended, however TMZ regimen may be adjusted at the discretion of the treating neuro-oncologist. Vaccine will always be given on day 21 ± 2 of each 28 day TMZ cycle. A CBC with manual differential (Lab Code 200640) and a T4/T8 ratio (2500202) will be obtained at the end of each cycle and on day of vaccine.

 CTC, common toxicity criteria (NCI)

| Table 3: Criteria to Resume Temozolomide after Radiation  |
|------------------------------------------------------------------|
| Absolute Neutrophil Count $\geq 1.0 \times 10^9/\text{L}$        |
| Platelet Count $\geq 100 \times 10^9/\text{L}$                   |
| Resolution of CTC Non-hematologic toxicities to Grade 2 or less. |

Because of the risk of opportunistic infections in patients receiving TMZ, patients may receive antibiotic prophylaxis at the discretion of the primary Neuro-Oncologist, consisting of inhaled pentamidine or oral levofloxacin. Antiemetic prophylaxis with metoclopramide or a 5-hydroxytryptamine3 antagonist will also be recommended before the initial doses of concomitant TMZ and may be used during the adjuvant five-day course of TMZ.

During TMZ cycles, dose adjustments to TMZ, if needed, will be conducted as outlined below:

| Table 4: Temozolomide Dose Reduction or Discontinuation During Maintenance Treatment |                                            |                          |
|---------------------------------------------------------------------------------------------|--------------------------------------------|--------------------------|
| Toxicity                                                                             | Reduce TMZ by 25 mg/m^2/d | Discontinue TMZ   |
| Absolute Neutrophil Count                                                                   | $<1.0 \times 10^9/\text{L}$                | See footnote a           |
| Platelet Count                                                                              | $<50 \times 10^9/\text{L}$                 | See footnote a           |
| CTC Non-hematological Toxicity (except for alopecia, nausea, vomiting)                      | CTC Grade 3                                | CTC Grade 4 a |

a: TMZ is to be discontinued if [dose reduction](#) to  $<50 \text{ mg/m}^2$  is required or if the same Grade 3 non-hematological [toxicity](#) (except for alopecia, nausea, vomiting) recurs after [dose](#) reduction.

[figure not shown]

#### **5.1.4 Leukapheresis**

Leukaphereses will be performed on each patient enrolled on this protocol. The leukapheresis will be used for immunologic monitoring. All leukaphereses will be between 2 to 4 hours long. It is estimated that 1.5 to 3 times the blood volume (~10-12 L) will be processed during this leukapheresis.

An additional 2-4-hour leukapheresis will be requested from patients with positive immunological responses to the therapy for additional immunologic monitoring studies.

PBMC will be obtained by leukapheresis at the Duke Apheresis Unit (SOP-JHS-HDC-CL-023 "Leukapheresis Collection Procedure") and transported to the Cell Processing facility (SOP-JHS-HDC-CL-011 "Leukapheresis Transport and Receipt Procedure"). For patients without sufficient venous access for leukapheresis a temporary intravenous catheter may be inserted.

#### **5.1.5 Daclizumab**

Patients in cohort # 1 will be randomized to receive daclizumab (1 mg/Kg) diluted in saline (FORM-JHS-CP-112 "Administration of Daclizumab"), or saline alone in the same manner. All patients that will receive daclizumab will get it at a 1 mg/Kg dose mixed with 50 mL of sterile 0.9% sodium chloride solution. Daclizumab solution will be administered in a peripheral or central vein over a 15-minute period. When mixing the solution, gently invert the bag in order to avoid foaming; do not shake. Infusion should be administered intravenously within four hours of preparation. If it needs to be held longer, it should be refrigerated between 2° and 8°C (36° to 46°F) for up to 24 hours after which it should be discarded. Medications for the treatment of severe hypersensitivity reactions including anaphylaxis should be available for immediate use. Patients will be monitored for anaphylactic events for 30 minutes.

Patients in cohort # 2 will receive daclizumab (1 mg/Kg) diluted in saline (FORM-JHS-CP-112 "Administration of Daclizumab") with vaccines # 1, vaccine # 3, and during the recovery from each TMZ cycle for first 3 cycles at the same dose.

### **5.2 Treatment Procedures**

#### **5.2.1 Vaccination**

After initial leukapheresis, all patients will then receive RT and concurrent TMZ at a standard targeted dose of 75 mg/m^2/d. Patients with progressive disease during radiation, dependent on steroid supplements above physiologic levels at time of vaccination, unable to tolerate TMZ or whose PBLs fail to meet release criteria will be replaced, but no more than 40 patients will be enrolled overall. Remaining patients will then receive the initial cycle of TMZ at a targeted dose of 100mg/m^2/d for 21 days 3 ± 1 weeks after completing RT and will be independently randomized to receive daclizumab versus saline simultaneous with vaccine #1. An additional cohort of 6 patients (cohort #2) will receive serial administrations of daclizumab during vaccine # 1, vaccine # 3, and during the recovery from each TMZ cycle for first 3 cycles at the same dose. Vaccine #1 will be given on day 21 ± 2 days after the start of the 100mg/m^2/d dose of TMZ. Each immunization will be divided equally to both inguinal regions. A total volume of 200 µL

per side will be delivered intradermally (SOP-JHS-HDC-CL-012 “Administration of Vaccine”). Details of the procedure will be recorded on the appropriate form (FORM-JHS-HDC-CL-012). Injection will be performed using a 1.5 inch 25 gauge needle. Due to the potential for particulates, CDX-110 final drug product should be filtered through a 5 micron filter needle (e.g., Becton Dickinson part no. 305200) prior to administration. The CDX-110/GM-CSF admixture should be injected as soon as possible after mixing. Prior to administration, 0.35 mL of GM-CSF will be withdrawn, under aseptic conditions, from the stock vial of Leukine® (500 mcg/mL) using a hypodermic needle and syringe. This 0.35 mL volume, containing 175 mcg GM-CSF, will be added aseptically to the vial containing 0.6 mL CDX-110, and mixed by gentle inversion of the vial (DO NOT SHAKE). After mixing, 0.8 mL of the CDX-110/GM-CSF admixture will be gently withdrawn (avoiding foaming and excess shearing) *using the provided filtration needle*, under aseptic conditions. The filtration needle should be removed and replaced with an appropriate needle for intradermal injection *before* the injection is administered to the patient. This 0.8 mL dose will contain approximately 500 mcg CDX-110 and 150 mcg GMCSF. Any remaining GM-CSF may be stored for up to 20 days at 2-8°C once the vial has been entered, and utilized for subsequent study drug administrations. Any remaining solution should be discarded after 20 days.

Patients will be monitored in the clinic for thirty minutes to one hour post-immunization for the development of any adverse effects. The immunization procedures will be supervised by a nurse or physician that has completed an Advanced Cardiac Life Support (ACLS) course. A cardiac resuscitation cart will be available in the immediate vicinity when performing these immunizations in case of severe allergic reactions. The initial three vaccines will be given each  $2 \pm 1$  week apart.

Patients will receive TMZ which will be delivered every 4 weeks. Therefore, in addition to the concurrent TMZ (75 mg/m^2/d) given with radiation, a total of 6 additional cycles of TMZ (100 mg/m^2/days 1-21) will be given. While standard dose 21-day TMZ treatment at a target dose of 100 mg/m^2/day is recommended, TMZ regimen may be adjusted at the discretion of the treating neuro-oncologist. Vaccine will always be given on day  $21 \pm 2$  of each 28 day TMZ cycle. Subsequent vaccines will be given on day  $21 \pm 2$  of each of the five remaining TMZ cycles. Cohort #2 will receive subsequent vaccinations along with daclizumab (1 mg/Kg) on day  $21 \pm 2$  for first 3 cycles. Vaccines will then continue monthly until progression. An additional leukapheresis will be required for any patients who have a positive DTH skin test for PEPvIII for immunologic monitoring.

If the TMZ cycles are completed without progression, monitoring will continue until clinical or radiographic progression without any additional prescribed antitumor therapy. During that time period, patients will be monitored clinically with routine physical and neurologic examinations and MMSE testing at every visit and with a contrasted-enhanced CT or MRI every  $8 \pm 4$  weeks. Peripheral blood will be obtained as outlined in the study flow sheet below for sub-clinical autoimmunity and immunologic monitoring.

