| Study Design:       | 
Twenty patients with newly-diagnosed EGFRvIII+ high grade glioma (WHO III or IV) will undergo leukapheresis for immunologic monitoring. Only 1 dose level of daclizumab (1 mg/kg) will be assessed. The decision to dose escalate in subsequent trials will be dependent on analysis of the safety and immunologic responses obtained in this trial. Patients will be followed until death. This study will be halted if any 2 patients experience a drug-related Grade IV or irreversible Grade III toxicity. After initial leukapheresis, all patients will then receive RT and concurrent TMZ at a standard targeted dose of 75 mg/m^2/d. Patients with progressive disease during radiation, dependent on steroid supplements above physiologic levels at time of vaccination, unable to tolerate TMZ or whose PBLs fail to meet release criteria will be replaced, but no more than 40 patients will be enrolled overall. Remaining patients will then receive the initial cycle of TMZ at a targeted dose of 100mg/m^2/d for 21 days <math>3 \pm 1</math> weeks after completing RT and will be independently randomized to receive daclizumab versus saline simultaneous with vaccine #1. An additional cohort of 6 patients (cohort #2) will receive serial administrations of daclizumab at vaccine # 1, vaccine # 3, and during the recovery from each TMZ cycle for the first 3 cycles at the same dose. Vaccine #1 will be given on day <math>21 \pm 2</math> days after the start of the 100mg/m^2/d dose of TMZ. While standard dose 21-day TMZ treatment at a target dose of 100 mg/m^2/day is recommended, TMZ regimen may be adjusted at the discretion of the treating neuro-oncologist. Vaccine will always be given on day <math>21 \pm 2</math> of each 28 day TMZ cycle. Vaccines will be given intradermally and divided equally to both inguinal regions. The calculated dosage of daclizumab will be administered in a 50 mL of sterile 0.9% sodium chloride solution via a peripheral or central vein over a 15 minute period. Vaccine #2 and #3 will occur at 2 week intervals. Patients will then be treated monthly with TMZ cycles for a total of 6 cycles after RT. TMZ will be given on days 1-5 of a 28 day cycle. Subsequent vaccines will be given on day <math>21 \pm 2</math> of each of the five remaining TMZ cycles. Cohort # 2 will receive subsequent vaccinations along with daclizumab (1 mg/Kg) on day <math>21 \pm 2</math> for first 3 cycles. Vaccines will then continue monthly until progression. An additional leukapheresis will be required for any patients who have a positive DTH skin test for PEPvIII for immunologic monitoring. Patients will be imaged after vaccine #4 and then bimonthly without receiving any other prescribed antitumor therapy until progression. Blood work for immunologic monitoring will be drawn before vaccine #1 and then each vaccine after vaccine #3. Blood work for sub-clinical autoimmunity will be drawn before vaccine #1 and every 4 months after vaccine #3. As part of standard care for these patients, upon tumor progression, participants may undergo stereotactic biopsy or resection. As this is not a research procedure consent will be obtained separately. However, if tissue is obtained, it will be used to confirm tumor progression histologically and to assess immunologic cell infiltration and EGFRvIII antigen escape at the tumor site.
 |

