### **3.2.2 Immunotherapy and Chemotherapy Combination**

Cancer vaccines can elicit tumor-reactive humoral and cellular immune responses. To date, these responses have not reliably been able to eliminate tumor, potentially due to the multiple immune suppressive mechanism present within the malignant environment. While it has been traditionally felt that chemotherapy would compromise the cellular elements necessary to generate immune responses, recent data suggest that perhaps chemotherapy can augment immune effects through either preferential elimination of regulatory components, or amplification of antigen exposure following cytotoxic cell damage (Emens, Machiels et al. 2001; Machiels, Reilly et al. 2001; Wheeler, Das et al. 2004; Chong and Morse 2005; Emens and Jaffee 2005; van der Most, Currie et al. 2006). In general, it appears that the immune system regenerating from a cytotoxic insult may be hyperacutely activated and particularly responsive due both to increased stimulatory cytokines within the environment and reduced regulatory elements. This protocol will give vaccination during the recovery phase of each maintenance chemotherapy cycle (day

21 of 28), allowing approximately 1 week for the immune activation prior to the initiation of the next cycle of temozolomide. (See IB for lymphocyte recovery data)

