### **3.12 TMZ-induced Lymphopenia and IL-2R $\alpha$ Blockade Enhance Immunity**

Therapeutic TMZ induces transient, Grade 3 lymphopenia (<500 cells/uL) in 70% of patients with GBM after the first cycle (150-200 mg/m^2/5d) with nadirs occurring 14-21 days after treatment (n=10). It also enhances the recovery of TRegs (Fig. 11). Thus, we evaluated TMZ for its capacity to induce homeostatic proliferation and to enhance antigen-specific immune responses in a murine model (Fig. 12 and 13). Markedly elevated levels of antigen-specific T-cells could be achieved and maintained in mice receiving antigen-specific vaccination after TMZ-induced lymphopenia when compared to normal hosts. Normal mice exhibited an increase of OVA-specific T cells from 0.49% to 1.90% of circulating CD8+ T cells one week post vaccination which subsequently contracted to 0.40% after two weeks, while TMZ pre-treatment resulted in an expansion from a frequency of 0.40% to 10.64% (absolute count increase from 3.41 cells/uL blood to 42.61 cells/uL) that continued to expand for 4 weeks post-vaccination to 21.18%. OVA-specific T cells in TMZ treated and vaccinated hosts were shown to be Th1-type memory/effector cells (CD44hiCD43loIFN- $\gamma$ +).

Anti-CD25 treatment (PC61), while having a negative impact on responses in normal mice, led to an even more dramatic enhancement of responses in TMZ treated mice (Fig. 12 and 13). PC61 pre-treatment alone had no effect in normal hosts. In contrast, in mice recovering from TMZ-induced lymphopenia, PC61 treatment given alone or in combination with vaccination significantly enhanced overall and antigen-specific T-cell expansion.

[figure not shown]

**Fig. 11:** TReg (%CD25+/FOXP3+ of CD45RO+/CD4+ T-cells) levels prior to TMZ and after each TMZ cycle. After staining PBMC surface antigens (CD45RO-FITC, CD25-PE, and CD4-PerCpP-Cy5.5, BD #555492, #555432, and #341654 respectively) cells are washed extensively and incubated on ice for 30 minutes in fixation/permeabilization buffer (eBioscience, #5123-43). Cells are then washed in 1X permeabilization buffer (eBioscience, #8333-56), pelleted, and stained with foxp3-APC (e Bioscience, #17-4776-73, clone PCH101). CD25+foxp3+ are gated from CD45RO+CD4+ lymphocytes. Values are an average of six donor sets representing pre through cycle 4.

[figure not shown]

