## 5 INVESTIGATIONAL PLAN

### 5.1 Preparation and Administration of Therapeutic Agents

#### 5.1.1 Overview

Twenty patients with newly-diagnosed EGFRvIII+ high grade glioma will undergo leukapheresis for immunologic monitoring. Only 1 dose level of daclizumab (1 mg/kg) will be assessed. The decision to dose escalate in subsequent trials will be dependent on analysis of the safety and immunologic responses obtained in this trial. Patients will be followed until death. This study will be halted if any 2 patients experience a drug-related Grade IV or irreversible Grade III toxicity. After initial leukapheresis, all patients will then receive RT and concurrent TMZ at a standard targeted dose of 75 mg/m^2/d. Patients with progressive disease during radiation, dependent on steroid supplements above physiologic levels at time of vaccination, unable to tolerate TMZ or whose PBLs fail to meet release criteria will be replaced, but no more than 40 patients will be enrolled overall. Remaining patients will then receive the initial cycle of TMZ at a targeted dose of 100mg/m^2/d for 21 days 3 ± 1 weeks after completing RT and will be independently randomized to receive daclizumab versus saline simultaneous with vaccine #1. An additional cohort of 6 patients (cohort #2) will receive serial administrations of daclizumab during vaccine # 1, vaccine # 3, and during the recovery from each TMZ cycle for the first 3 cycles at the same dose. Vaccines will be given intradermally and divided equally to both inguinal regions. The calculated dosage of daclizumab will be administered in a 50 mL of sterile 0.9% sodium chloride solution via a peripheral or central vein over a 15 minute period. Vaccine #2 and #3 will occur at 2 week intervals. Patients will then be treated monthly with TMZ cycles for a total of 6 cycles after RT. TMZ will be given on days 1-21 of a 28 day cycle. While standard dose 21-day TMZ treatment at 100 mg/m^2/day is recommended, the TMZ regimen may be adjusted at the discretion of the treating neuro-oncologist. Vaccine will always be given on day 21 ± 2 of each 28 day TMZ cycle. Subsequent vaccines will be given on day 21 ± 2 of each of the 5 remaining TMZ cycles. Cohort #2 will receive subsequent vaccinations along with daclizumab (1 mg/Kg) on day 21± 2 for first 3 cycles. Vaccines will then continue monthly until progression. An additional leukapheresis will be required for any patients who have a positive DTH skin test for PEPvIII for immunologic monitoring. Patients will be imaged after vaccine #4 and then bimonthly without receiving any other prescribed antitumor therapy until progression. Blood work for immunologic monitoring will be drawn before vaccine #1 and then monthly after vaccine #3. Blood work for sub-clinical autoimmunity will be drawn before vaccine #1 and every 4 months after vaccine #3. As part of standard care for these patients, upon tumor progression, participants may undergo stereotactic biopsy or resection. As this is not a research procedure consent will be obtained separately. However, if tissue is obtained, it will be used to confirm tumor progression histologically and to assess immunologic cell infiltration and EGFRvIII antigen escape at the tumor site.

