#### **9.2.5      Delayed Autoimmune Diseases**

It is possible that delayed autoimmune disease(s) may develop as a result of injection with CDX-110. This means that the immune system may be stimulated to attack natural tissue in the body. Animal studies have reported the development of autoimmunity in the context of vaccination and recovery from lymphopenia. However, our current experience with CDX-110 vaccination in glioma patients has not demonstrated evidence of autoimmunity in treated patients. Furthermore, the doses of TMZ used in this study for induction of lymphopenia are standard doses administered to patients with GBM. It therefore, is unknown what the risk of delayed autoimmune disease is for this study.

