| Initial Temozolomide Cycle                                 | 3 ± 1 week post RT (Days 1-5) |                                                             | X                                                                     | X    |                                                                                                             |                   | X                          |                                          |
| Immunization #1 (Daclizumab)                               | Day 21 ± 2                    |                                                             | X                                                                     |                   | X                                                                                                           |                   | X                          |                                          |
| Immunization #2                                            | Day 35 ± 7                    |                                                             | X                                                                     |                   |                                                                                                             |                   | X                          |                                          |
| Immunization #3(Daclizumab cohort#2)                       | Day 49 ± 7                    |                                                             | X                                                                     |                   |                                                                                                             | X                 | X                          |                                          |
| Temozolomide Cycles                                        | Every 4 weeks (Days 1-5)      |                                                             |                                                                       |                   |                                                                                                             |                   | X                          |                                          |

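### On the recommended 21-day temozolomide schedule, day 21 ± 2 puts vaccine #1 and daclizumab at the end of dosing, not in the off-drug recovery phase the protocol describes

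*Protocol*

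**What the plan says.** **Temozolomide schedule.** Sections 5.1.1, 5.1.3 and 5.2.1 recommend 100 mg/m²/d on a 21-day schedule. Section 5.1.1 puts it as "TMZ will be given on days 1-21 of a 28 day cycle". The same sections let the treating neuro-oncologist change the regimen.

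**Immunisation day.** Section 5.2.1 says "Vaccine #1 will be given on day 21 ± 2 days after the start of the" 100 mg/m²/d dose, and cohort 1 is randomised to daclizumab or saline given with that vaccine. Day 21 ± 2 of each 28-day cycle applies whatever regimen is chosen.

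**Intended phase.** Section 3.2.2 reads "This protocol will give vaccination during the recovery phase of each maintenance chemotherapy cycle (day" 21 of 28). Section 5.1.5 ties cohort 2's later daclizumab doses to recovery from each of the first three cycles, while Section 5.2.1 puts those doses on day 21 ± 2. The hypotheses and the primary objective (Sections 2.1 and 2.2.1) concern TReg recovery after temozolomide-induced lymphopenia.

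**Five-day wording that remains.** For the monthly cycles the synopsis says "TMZ will be given on days 1-5 of a 28 day cycle", although it gives the initial cycle as 21 days. The flow sheet (Section 11) lists days 1-5 for the initial cycle and, for later cycles, "Every 4 weeks (Days 1-5"). The antiemetic text in Section 5.1.3 says treatment "may be used during the adjuvant five-day course of TMZ".

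**The concern.** A fixed immunisation day describes a phase of the cycle only if the dosing days are also fixed. Here the body of the protocol recommends dosing up to day 21 and immunises on day 21, yet calls that day recovery. Day 21 is clearly off drug only under the days 1-5 schedule that survives elsewhere in the document.

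The protocol itself treats timing as important. Section 3.11 holds that what IL-2Rα blockade does depends wholly on the setting in which it is given. Section 3.12 reports opposite effects of anti-CD25 in normal mice and in mice recovering from temozolomide.

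Two things are at stake. One is whether conclusions about recovery describe what was done. The other is whether patients within one arm of 10 receive the randomised drug at different points of depletion, with no regimen term in the primary model of Section 8.2.1.

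**Working it through.** The check is a day count. The protocol states no figure of its own to reproduce.

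**Inputs.** The last temozolomide day is 21 (Sections 5.1.1 and 5.2.1) or 5 (flow sheet, and the synopsis for monthly cycles). The window is 21 ± 2. It can be read as the day of the cycle, with the start as day 1 (cycle days 19 to 23). It can also be read as days after the start (cycle days 20 to 24).

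**Formula.** Days from last dose = immunisation day − last dosing day.

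| Schedule | Reading of the window | Cycle days | Days from last dose | On or before last dose | After it |
|---|---|---|---|---|---|
| 21-day | day of cycle | 19-23 | 19−21 = −2 to 23−21 = +2 | 3 of 5 | 2 of 5 |
| 21-day | days after start | 20-24 | 20−21 = −1 to 24−21 = +3 | 2 of 5 | 3 of 5 |
| 5-day | day of cycle | 19-23 | 19−5 = 14 to 23−5 = 18 | 0 of 5 | 5 of 5 |
| 5-day | days after start | 20-24 | 20−5 = 15 to 24−5 = 19 | 0 of 5 | 5 of 5 |

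**Spread within an arm.** Two patients immunised on the same cycle day, one on each schedule, differ by 21 − 5 = 16 days from last dose. Across the cycle-day window the difference runs from 14 − 2 = 12 to 18 − (−2) = 20 days. The number of patients who would leave the 21-day regimen is not given, nor is the dependence of the TReg assay on time from last dose. The added variance therefore cannot be computed.

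**Time to the next cycle.** Without a delay the next cycle starts on day 29, which is 29 − 21 = 8 days after day 21 under either schedule. Section 3.15.2 delays the second maintenance cycle by 1 to 3 weeks. That moves its start to day 36 to 50, or 15 to 29 days after day 21.

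**The case against.** A reader might infer that the trial cannot test inhibition of TReg recovery, or that daclizumab is always given on or before the last dose. The documents do not support either reading.

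- Two or three of the five permitted days fall after the last dose, depending on the count.
- The protocol never defines when recovery begins and shows no lymphocyte kinetics for 21-day dosing.
- An antibody present as dosing ends could act while recovery proceeds. In the mouse model of Section 3.12 anti-CD25 was given 48 hours after temozolomide. In monkeys (Section 3.13) depletion was delayed and lasted more than 4 weeks. The delayed second cycle leaves roughly two to four drug-free weeks after vaccine #1.

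A reader might also infer that day 21 was derived from the five-day data of Section 3.12, "with nadirs occurring 14-21 days after treatment (n=10"). No passage says so. Section 3.2.2 refers to the investigator's brochure for lymphocyte recovery, which is not at hand, and its interval of about a week before the next cycle holds on both schedules. Nor do those data show that a five-day course would meet the recovery description. Counted from the last dose, the nadir covers cycle days 5 + 14 = 19 to 5 + 21 = 26, which includes day 21.

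Finally, cohort 1 is randomised under one timing rule, so differences in regimen are not a source of systematic bias.

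All of this stands and limits the point. It does not remove the mismatch between the recommended schedule, the immunisation day and the recovery wording. It also does not explain how cohort 2's doses can be both on day 21 ± 2 and in recovery from a cycle whose dosing ends on day 21.

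**Conclusion.** The point holds as an inconsistency that should be fixed; it does not invalidate the design. On the recommended 21-day schedule the infusion falls within 2 days of the last temozolomide dose (3 days on the alternative count). That is the end of dosing, not the off-drug phase Section 3.2.2 describes. On the remaining five-day wording the same day is 14 to 18 days after the last dose (15 to 19 on the alternative count).

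Because the regimen may be changed while the day may not, timing relative to the last dose can differ by about two weeks between patients in one arm. The consequence for the primary comparison is possible extra variance and chance imbalance, of unknown size, with 10 patients per arm. This rests on two assumptions: that dosing follows the schedules as written, and that some patients actually receive a different regimen. If every patient stayed on 21 days, the variance argument would fall away and the wording conflict would remain.

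**What to change.** 1. **Reconcile the text.** Make the temozolomide schedule, the immunisation day and the recovery wording agree across the synopsis and Sections 3.2.2, 5.1.1, 5.1.3 (including the antiemetic sentence), 5.1.5, 5.2.1 and 11. Which schedule or day applies is for the clinical team.
2. **Record and use the regimen.** Record the cycle 1 regimen chosen before randomisation and include it in the TReg comparison as a covariate or a sensitivity term. For two arms with 20 patients this takes residual degrees of freedom from 20 − 2 = 18 to 17 at a given PHA level.
3. **Report the timing.** By arm, give days from last temozolomide dose to vaccine #1 and the lymphocyte count on that day. These are best kept descriptive, since the actual day may be set after randomisation.
4. **Word conclusions to match.** State when daclizumab was given relative to temozolomide wherever a result is described as concerning recovery.

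The cost is protocol wording, recording of regimen and last-dose date, and about one degree of freedom. Blood counts with differential are already drawn on the day of vaccination (Sections 5.1.3, 6.2.1 and 6.2.4).
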